### Allocation and masking

The randomization unit is the individuals participating in the trial. A random allocation is made within a 3-tiered stratification based on the number of doses of vaccine required for successful immunization (1, 2 or 3 doses). Within each tier, simple randomization is performed by spreadsheet, in an attempt to control the confounder effect of the number of doses.

Mapping is performed by the Fundación Galicia Sur (EOXI Vigo) to which all researchers were given telephone access.

Information concerning the randomization process remained confidential until the end of the study. It is the responsibility of each researcher to ensure that there is a specific procedure that allowed for the opening of the code in case of emergency, with immediate communication to the randomization centre.

The route of administration is masked in the database to prevent the team performing the computer analysis from discovering the route that corresponded to each group.

Loss of masking only occurred in cases of emergency for the patient and at the conclusion of the study.

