## Methods/design

We present a prospective, double-blind, phase IV clinical trial with two parallel groups and layered randomized assignment. Each one of these parallel groups was given doses of the corresponding tetanus vaccine, either intramuscularly (Group 1) or subcutaneously (Group 2), as shown in Figure 1. The layers were defined by the number of doses of the corresponding anti-tetanus injections (one, two or three), in each tier. This trial was only designed for the vaccination of the general anticoagulated population, and not for situations with wounds.

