### Sample size

Assuming that for the IM route the percentage of local side effects is 30% [11, 15, 16] and expecting an increase of 18% [15] in local secondary effects for the alternative route (SC), using a bilateral approach, with a 95% confidence interval, a beta risk of 0.20 requires 115 patients in each group. Taking into account the possible 15% loss in information, the final sample size was 135 patients in each group. With this sample size, it was estimated that a 3 UI/ml mean difference in antibody levels could be detected.

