After assessing if the patient fulfilled all inclusion criteria, and none of the exclusion criteria, they were invited to participate in the study and, if they agreed to sign informed consent, were included in one of the tiers, according to the corresponding (allocation ratio 1:1) vaccine dose (one, two or three). The patients were given an appointment to have an INR test and, if the score was less than 4, a blood sample was taken to determine anti-tetanus antibodies, and a dose of vaccine was immediately administered, so that the patient could proceed to the corresponding nursing consultancy. The nurse was responsible for requesting from the randomization centre, by telephone, the administration route to which the patient had been assigned*.* The patient was not informed of the administration route used*.* Patients requiring more than one dose received all doses via the same route, and were given appointments in relation to the interval and number of corresponding doses.

The doctor was blinded to the administration route and also to the follow-up appointments (1, 2, 14 and 30 days) after each dose of the vaccine to detect any side effects.

On the first visit, after administering the vaccine, and at 30 days after the last dose of anti-tetanus vaccine (ATV), the antibody titre was determined for all patients using enzymatic immunoanalysis.

The systematic physical examination at each visit included the following aspects:

 General appearance. Temperature Arterial blood pressure. Measurement of the brachial perimeter at the height of the deltoid on the first visit, and at the site of inoculation after vaccination. Examination and palpation of the injection site looking for basic injuries. Homolateral axillary palpation of the injection site. Any examination required due to the emergence of a general and/or unexpected side effect.

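### Simple randomisation inside each dose tier balances the number of doses no better than unstratified tossing, so the allocation does not deliver the control it is meant to give

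*Protocol article*

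**What the plan says.** The Methods/design section describes a "phase IV clinical trial with two parallel groups and layered randomized assignment", with layers defined by the number of doses the patient needs (one, two or three). The Allocation and masking section repeats the three tiers and then fixes the method and its aim: "Within each tier, simple randomization is performed by spreadsheet, in an attempt to control the confounder effect of the number of doses". The Interventions section gives a 1:1 ratio. No section mentions blocks, minimisation or fixed numbers per tier.

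In the Statistical analysis section the tiers appear in the descriptive classification within each route. The comparisons named there are:

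- chi-squared, Student's t and Mann–Whitney tests between the two routes;
- a relative risk by a Mantel-type method, not said to be stratified by tier;
- a logistic regression for safety, intended to control confounding covariables, which are not listed.

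No tier-adjusted comparison of antibodies is stated.

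**The concern.** Stratified randomisation balances a factor only when assignment inside each stratum is restricted. Drawing independent tosses from three tier lists rather than one changes nothing about how many one-, two- or three-dose patients reach each route. The article therefore credits the allocation with a control that it cannot supply.

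Number of doses is likely to be prognostic for both outcomes. The article calls it a confounder. Side effects are sought after every dose, so three-dose patients have more occasions to react. Patients due a booster and patients starting primary vaccination also have different vaccination histories before their titres are measured. A chance difference in tier mix then moves an unadjusted route comparison, and it adds noise that restricted allocation or a tier-adjusted analysis would remove.

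**Working it through.** **1. The plan's own figure.** The Sample size section assumes 30% local effects intramuscularly and 18 points more subcutaneously (48%), and states: "using a bilateral approach, with a 95% confidence interval, a beta risk of 0.20 requires 115 patients in each group". With p̄ = 0.39:

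n = [1.96·√(2·0.39·0.61) + 0.842·√(0.30·0.70 + 0.48·0.52)]² / 0.18² = 114.1, rounded up to 115.

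This reproduces the stated figure. Allowing for 15% loss, 115/0.85 = 135.3; the article uses 135 per group, 270 in all. It gives no figure for balance, so the rest is derived.

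**2. Equality of the two schemes.** In a tier of n patients, the number allocated to one route is Binomial(n, 0.5) under either scheme, independently across tiers. The SD of the difference between routes is √n. Tier sizes are not given, so those below are assumptions; the equality does not depend on them. Results are from 200,000 simulated trials of 270 patients:

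| Tier sizes | Chance that any tier splits 60:40 or worse: simple within tiers | Unstratified simple | Blocks of 4 within tiers |
|---|---|---|---|
| 90/90/90 | 0.20 | 0.20 | 0 |
| 54/54/162 | 0.257 | 0.257 | 0 |
| 27/27/216 | 0.435 | 0.435 | 0 |

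With 90/90/90, the 95th percentile of the difference between routes in a tier's share is 11.4 points under both simple schemes and 1.5 points with blocks of 4. The SD of the difference in patient numbers per tier falls from 9.5 (= √90) to about 1.2.

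**3. Effect on the crude risk difference (illustration).** Assumptions: half the patients need three doses and the other half one; reactions are independent across doses; the overall intramuscular rate is the planned 30%.

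- Per-dose risk p solves 0.5·p + 0.5·[1 − (1 − p)³] = 0.30, so p ≈ 0.171. The tier rates are about 17% and 43%, a gap of 0.259.
- SD of the difference in three-dose share between routes: √(2·0.5·0.5/135) = 0.061, or 6.1 points; 95% limit 1.96 × 6.1 = 11.9 points.
- Shift at one SD: 0.061 × 0.259 = 1.6 points. At the 95% limit: 0.119 × 0.259 = 3.1 points.

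Over a range of three-dose shares, with the same equation weighted accordingly:

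| Three-dose share | One- and three-dose rates | 95% limit of share difference | Shift at 95% limit |
|---|---|---|---|
| 20% | 24%, 55% | 9.5 points | 3.0 points |
| 50% | 17%, 43% | 11.9 points | 3.1 points |
| 80% | 13%, 34% | 9.5 points | 2.0 points |

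**4. Loss of precision.** The SE of the crude difference is √[(0.30·0.70 + 0.48·0.52)/135] = 5.8 points, a 95% half-width of 11.4 points. In the half-and-half case tier explains 0.25 × 0.259² / 0.21 = 8% of the outcome variance. Perfect balance would therefore shrink the SE by about 1 − √0.92 = 4%.

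**The case against.** The strongest defence is that nothing here is biased. Chance tier imbalance under simple randomisation is already part of the sampling variance of the crude comparison, so the tests keep their error rate. That stands. A reader might infer that the route comparison is confounded or the planned tests invalid; the article gives no ground for that.

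A reader might also want a larger shift, by taking 30% as the one-dose rate and 1 − 0.7³ = 66% as the three-dose rate. With half the patients in each, that implies about 48% overall intramuscularly, whereas the Sample size section uses 30% for the whole group. The smaller figures above are the ones consistent with the plan. Positive correlation of reactions within a patient would lower them further.

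Unequal total arm sizes do not bear on dose balance, and they cost little: with 270 evaluable, power is 86.2% at 135/135 and 85.7% at 119/151.

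On the analysis, it would be too strong to say that number of doses is ignored. The safety regression is meant to control confounders, the article names number of doses as one, and a covariate list can properly sit in an analysis plan that is not shown. This softens the consequence for safety. For antibodies, however, the article describes only unadjusted comparisons between routes, and no later adjustment would make the statement about the allocation true.

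The article's wording is of an attempt rather than a guarantee. That is fair, but the attempt adds no balance at all. If the spreadsheet in fact held lists with equal numbers per tier, the method would be sound and its description wrong; the article does not say so.

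**Conclusion.** The point holds in a limited form. As described, the allocation does not control the number of doses, and this follows from the method alone, without any assumption about tier sizes. The consequence is moderate: unbiased allocation and valid crude tests, with avoidable chance imbalance that is worst in small tiers and a few per cent of precision lost. The illustrative shift of about 1.6 points at one SD and about 3 points at the 95% limit rests on assumed tier shares, independence of reactions across doses and the planned 30% rate. It is a chance displacement in either direction, and should not be read as a bias to set against the 18-point effect. The correction is worth making because it is cheap and the tiers are already recorded.

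**What to change.** - **Safety:** make the main route comparison by randomised tier, either as a tier-stratified Mantel-type relative risk or with tier as a named term in the logistic regression.
- **Antibody increase:** make the main route comparison adjusted for, or stratified by, randomised tier.
- **Reporting:** give the number of patients by route and tier.
- **Wording:** in the Allocation and masking section, either state the restriction if one was used, or drop the suggestion that the allocation controls the number of doses and say that the analysis does so.
- **Allocation still open, if any:** use permuted blocks of varying size within tiers, held at the existing telephone centre. The Data collection section reports first inclusion in January 2009 and a period extended to 72 months, so this probably comes late.

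The sample size does not change. The analysis and wording changes need no new data. Blocks need a new list and bring slight predictability, limited by varying block sizes and central allocation.

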### Ethical aspects and confidentiality of data

In compliance with the Helsinki Declaration, it was the responsibility of the researcher to inform the patients of their participation in a clinical study, and to clarify that this participation was voluntary and did not imply any change in treatment or medical care received by participating patients, as compared to that received by patients who did not participate. The researcher then had to obtain written, informed consent from patients before they could be included in the study.

The highest levels of confidentiality and professional conduct were always maintained and the existing national legislation on data protection was respected. The patients’ identities were encoded in the study documents and only duly authorized personnel had access to identifiable personal data, when data verification procedures required that this information had to be inspected.

It was the responsibility of the researcher to inform the patients in a clear and concise way that their data would be incorporated into a computerised database, which would only be used for clinical research purposes, and that the patient could not be identified in that database. In the database, the patients were each assigned an internal code number by the randomization centre, which remained unknown to the researcher, so that their clinical data could not be associated to the identified or identifiable person.

Likewise the CRF data were treated confidentially. The name of the patient was hidden and could only be identified through a number corresponding to the researcher code and the patient code.

This project respected ethical principles for medical research involving human subjects, as set out in the World Medical Association Declaration of Helsinki, together with the clinical research rules of the Spanish Research Act Regulations, and was granted permission by the Clinical Research Ethics Committee with approval obtained on 07/06/2007 with number 2007/089 (N° EudraCT 2007-001073-29), which was subsequently modified and extended on 13/04/2009, 10/09/2009 and 13/12/2010 by successive expansion in the number of participating health centres (from the initial 6 to 15), to improve recruitment of patients.

During the development of the study, there was regular monitoring that the information contained in each patient’s CRF was complete and regularly updated, and that the required good clinical practice was being maintained in adherence with the Protocol and the follow-up procedures.

The original documents of each participating patient in the study, consisting of annotations made during each visit and the signed original of informed consent forms, were maintained by the researchers.

## Discussion

This present clinical trial was designed to demonstrate that the administration of tetanus vaccine via the intramuscular route is safe and has greater efficacy than the subcutaneous route in anticoagulated patients, which would make it possible to routinely recommend this route in these patients. This is relevant because the prevalence of patients treated with oral anticoagulants is increasing, even at younger ages, and anti-tetanus vaccine, the only one with universal indication, is still the only measure with proven efficacy for preventing new cases of tetanus.

There are inherent difficulties in conducting clinical studies, with a variety of possible eventualities that affect researchers, patients and the actual structure and organization of the centres. To these handicaps, must be added the following particular characteristics of primary care: the extra effort required for coordination given the scattering of the centres and researchers; the accessibility of care at this level, at least in Spain, which causes great pressure on health and welfare services with little control over the distribution of daily work, with a resulting conflict regarding the space and time available for research activities.

In addition, there are problems relating to the study itself. For example, as the number of anticoagulated patients with vaccination criteria is low, to obtain a viable study population sample size required the participation of a large number of centres, which hindered the monitoring and coordination of the project. Finally, the large number of participating centres increased the need for special care in keeping doctors and patients blind to the route of vaccination.

## Abbreviations

Td: Tetanus-diphtheria (vaccine)
IM: Intramuscular
SC: Subcutaneous
INR: International normalized ratio
CRF: Case report form
NNT: Number (of patients) Needed to be Treat to prevent an event
ITT: Intention-to-treat (analysis)
RAR: Reduction of absolute risk.
